### Blinding

All participants, investigators, hospital pharmacist, project inspectors, statisticians and other staff will be blinded to the treatment assignment of the participants. The researchers of the Clinical Evaluation Centre will be responsible for blinded pairing of drugs and participants and will keep emergency envelopes to be opened in the event of medical emergency or severe adverse events during the trial.

### Sample size

Due to the lack of preliminary studies on the evaluation of the efficacy of XFZYC for QS&BSS using the traditional Chinese medicine patient-reported outcome (PRO) scale, we could not calculate the appropriate sample size. Therefore, we adopted this pilot study with an appropriate sample size of 60 participants per group. The outcomes of this trial will provide data support for the calculation of the appropriate sample size for future clinical trials.

### Intervention

The participants in the test group will take six granules of XFZYC (0.4 g/granule) twice a day for 7 weeks. The participants in the control group will take six granules of an XFZYC-simulated agent (0.4 g/granule) twice a day for 7 weeks. All drugs will be taken orally after meals. The XFZYC and XFZYC-simulated agents will be provided by Tianjin Hongrentang Pharmaceutical Co., Ltd., Tianjin, China. Although the colour and smell of the contents of XFZYC and XFZYC-simulated agents are not identical, the capsule shell makes the drugs seem less different. All the drugs are concealed in the same sealed and opaque packages. The label of the package contains the drug name, the approval number, functions, usage, dosage, storage conditions, expiration date, and the name of the manufacturer. Participants will be informed that they would be randomly assigned to receive either XFZYC or XFZYC-simulated agents. They will be encouraged to contact the investigators if they have any uncomfortable feeling or if they think the drugs are not helpful. Participants in both groups can continue their prior routine treatments, with the exception of Chinese herbal medicine. The details of these routine treatments will be recorded in the case report forms (CRFs). Details of the study procedures are shown in Fig. 1.

**Fig. 1 Fig1:**
[figure not shown]
Content for the schedule of enrolment, interventions and assessments. CRF, case report form

### Outcome measures

The primary objective of this trial is to assess the feasibility and acceptability of a range of outcome measurements to determine the appropriate ones for future definitive trials. Data completeness ≥ 80% is required for an outcome to be considered for definitive trials. Reported and recorded values will be considered complete, while unknown and bland values will be considered missing:The enrolled participants will be provided with the traditional Chinese medicine PRO scale to assess the change in the clinical symptoms of QS&BSS [21] (http://kns.cnki.net/) (See Additional file 3: Table S2).Each patient’s single symptom and sign evaluation will use the score of the single symptom and sign scale of QS&BSS (See Additional file 3: Table S3). According to the degree of symptoms and signs, the score will be assigned as follows: no = 0; mild = 1; moderate = 2; or severe = 3 [22].Pain levels will be assessed using the score of the pain scale of QS&BSS (See Additional file 3: Table S4). The total score includes a visual analogue scale pain index [23] and the score of degree, duration, and frequency of pain [24]. The location of the pain will be recorded independently.

Each of the above scales will be completed on the day of enrolment and at the 2nd, 4th, 6th, and 7th weeks. Among the multiple time points for the measurements, we will mainly focus on the data from the day of enrolment and the 7th week, which are the intended measurement time points according to previous studies. Additionally, we will observe the “inflexion point”, which refers to the time point when the clinical symptoms of QS&BSS changes during the intervention, to optimise the measurement time point for an adequately powered definitive trial in the future.

### Safety and adverse events

Participants will receive the following tests on the day before enrolment and the day after completion of the intervention period:Physical examination (temperature, respiration, heart rate, blood pressure, height, and weight)Electrocardiogram (ECG)Complete blood cell countCoagulation function (prothrombin time (PT), activated partial thromboplastin time (APTT), thrombin time (TT), fibrinogen (FIB), D-dimer, INR)UrinalysisFaecal occult blood testLiver function (ALT, AST, alkaline phosphatase (ALP), serum total bilirubin (STB), and γ-glutamyl transpeptidase (γ-GT))Renal function (creatinine (Cr), blood urea nitrogen (BUN), and urine N-acetyl-β glucosaminidase)

Any adverse events will be recorded in a CRF with details, including occurrence time, severity, duration, effective measures and the outcomes. According to the judgement of severity, the investigators will determine whether the participants should be suspended or withdrawn from the trial. When SAEs occur, such as severe haemorrhage, hepatic failure, renal failure or death, the investigator will report to the principal unit and ethics committee, and the investigator can open the patient’s emergency envelope to determine the group allocation.

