##### Suspension criteria

The study may be suspended for the following reasons:Non-cooperation of the participants during the trial for any reasonThe decision to suspend the study by CFDA or other authorityOccurrence of serious adverse events (SAEs)Discovery of a deviation in the protocol

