### Data management and statistical analysis

The clinical data management system (http://www.tcmcec.net/) will be used to collect and manage the data. All data from the completed CRFs will be imported into the system twice by two independent data entry clerks to ensure the accuracy. The database will be locked when the principal investigators and statisticians check the data. The original medical records will be archived and saved in the unit responsible for 5 years after the completion of the trial.

All statistical analyses will be performed by an independent statistician blinded to the allocation, using the Statistical Analysis System (SAS, Version 9.2, Institute Inc., Cary, NC, USA) and assuming a two-sided test and a 0.05 level of significance. Based on the strict principle of intention-to-treat (ITT), the outcome measurements will be analysed using a full analysis set (FAS), which means the data of the participants will be analysed according to their original allocation, regardless of the treatment they actually received, withdrawals, losses to follow up, or crossovers. The last-observation-carried-forward (LOCF) method will be used for missing data, and safety outcomes will be analysed using safety sets (SS). Quantitative data will be analysed using the *t* test and analysis of variance (ANOVA). Enumeration data will be analysed using the chi-square test or non-parametric tests. We will use the paired *t* test to analyse significant differences between pre and post treatment. The total dropout rate in each group will be analysed using the chi-square test or Fisher’s exact test. Moreover, the reasons for dropouts will also be descriptively analysed and compared between the two groups. For the safety analysis, the incidence rate of adverse events will be evaluated using the chi-square test and described in a list.

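### The stated exit rules tie stopping the drug to leaving the trial, and nothing keeps participants who stop the drug under assessment, so off-drug scores on all three scales can be lost

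*Protocol article*

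**What the plan says.** All places are in the protocol article.

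- **Safety and adverse events.** Depending on severity, "the investigators will determine whether the participants should be suspended or withdrawn from the trial". The exit named is from the trial. Stopping only the drug is not listed, and suspension of a participant is not defined.
- **Rejection criteria.** Refusing the trial drug and not wishing to go on with the trial are two separate items. The second can only describe someone already taking part, so the list reaches enrolled participants. The section does not say what rejection leads to.
- **Suspension criteria.** The list opens at study level: "The study may be suspended for the following reasons". Some of its items concern single participants (non-cooperation, serious adverse events). It sets no follow-up after drug stop.
- **Intervention.** Of the participants it says: "They will be encouraged to contact the investigators if they have any uncomfortable feeling or if they think the drugs are not helpful".
- **Outcome measures.** "Each of the above scales will be completed on the day of enrolment and at the 2nd, 4th, 6th, and 7th weeks". The feasibility limit is "Data completeness ≥ 80% is required for an outcome to be considered for definitive trials", with the definition "Reported and recorded values will be considered complete, while unknown and bland values will be considered missing". No denominator is given.
- **Data management and statistical analysis.** Participants are analysed as allocated, "regardless of the treatment they actually received, withdrawals, losses to follow up, or crossovers". For gaps, "The last-observation-carried-forward (LOCF) method will be used for missing data". Dropout rates and reasons are compared between the arms.
- **Quality control.** Late takers are encouraged, withdrawals and compliance are recorded, and extra visits and follow-ups serve to hold dropout within 20%. The section does not say that this covers people withdrawn or rejected.

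**The concern.** Stopping a drug and leaving a trial are different events, and an analysis by allocation needs scores after the first as long as the second has not happened. Here the adverse-event rule offers an exit from the trial, and the rejection list catches someone who refuses capsules but would still fill in the scales. Because participants are invited to report discomfort or lack of benefit, reasons tied to tolerability or effect can be expected to come up.

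Two things are at stake. First, the week-7 score of such a participant would be replaced by one taken on treatment or shortly after it. Second, the primary objective is the feasibility of the outcome measures, and the only numerical limit for it is the 80% completeness rule. A score lost because of the drug says nothing about whether the scale is acceptable, yet it may count against that scale.

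**Working it through.** The article states no figure on this point, so there is none to reproduce. The check is a reading of the text, followed by an illustration of size.

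**1. Text.** The question is whether any section separates drug stop from trial exit. Safety and adverse events names exit from the trial. Rejection criteria make drug refusal a ground of its own. Outcome measures schedule the scales but do not mention drug stop. The analysis section governs how data are used, not whether they are collected. Quality control describes general retention. None provides for stopping the drug and keeping the assessments.

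**2. Records at stake.** There are four post-baseline visits (weeks 2, 4, 6, 7) and three scales, so 4 × 3 = 12 records per participant. Someone who leaves just after week 2 loses 3 × 3 = 9 of the 12.

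**3. The 80% rule.** Inputs from the article: 120 participants and a limit of 80%. Required: 0.80 × 120 = 96 complete, so 120 − 96 = 24 may be missing. The dropout ceiling in Quality control, 20% of 120 = 24, equals that whole allowance.

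Assumptions, none from the article: completeness is judged at week 7 over all 120, losses add, and participants are independent. With p = 1 − other loss − loss after drug stop, the chance of meeting the rule is P(X ≥ 96), where X is binomial(120, p).

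| Leave after drug stop | Other loss 5% | Other loss 10% | Other loss 15% |
|---|---|---|---|
| 0% | p = 0.95: 1.00 | p = 0.90: 1.00 | p = 0.85: 0.95 |
| 2% | p = 0.93: 1.00 | p = 0.88: 1.00 | p = 0.83: 0.84 |
| 5% | p = 0.90: 1.00 | p = 0.85: 0.95 | p = 0.80: 0.55 |

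Solving P(X ≥ 96) = 0.90 gives p = 0.8393, a total loss of 16.1%. The room left for other loss is therefore 16.1% if nobody leaves after drug stop, 16.1 − 2 = 14.1% if 2% leave, and 16.1 − 5 = 11.1% if 5% leave. If losses multiply instead of adding, 15% other loss and 5% leaving give p = 0.85 × 0.95 = 0.8075 and a probability of 0.635 in place of 0.554.

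**4. LOCF.** Shift of an arm mean = fraction leaving × (carried score − week-7 score they would have had). Assume 2% to 5% of one arm leave (about 1 to 3 of 60) and the difference is 0.5 to 1 SD:

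- 0.02 × 0.5 SD = 0.01 SD
- 0.05 × 0.5 SD = 0.025 SD
- 0.05 × 1 SD = 0.05 SD

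Equal losses and differences in the two arms would cancel in the comparison.

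**The case against.** The strongest reply is that this is silence in a condensed article: the text never says that visits stop, and follow-up detail may sit in the full protocol. That stands in part. It does not remove the point, because the article does state rules, namely exit from the trial after an adverse event and rejection for refusing the drug, and it is those rules that are questioned.

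*Suspended* may already mean a drug pause with visits kept, and withdrawal is permitted, not required. Both are fair. The term is undefined, so defining it is part of the remedy. The rejection list also contains an item on having no record to evaluate, so it may concern who is evaluable and not when visits end. That reading is possible and weakens this half of the point.

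The scales are scheduled without reference to drug intake, the analysis is by allocation, and Quality control aims to retain people. These lean towards continued assessment, but none says so for participants who stop the drug.

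Some stronger conclusions might be drawn, and the article does not support them:

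- *Assessments end when the drug is stopped.* No section says this. The rules allow it; they do not order it.
- *The intention-to-treat statement is contradicted.* It concerns analysis, not collection. It is poorly served, not broken.
- *Withdrawn participants count as missing against the 80% limit.* No denominator is given. If completeness refers only to forms that were administered, they may not count, and the table above does not apply.
- *The choice between scales is distorted.* All three scales lose the same participants, so their comparison is little affected.

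**Conclusion.** The point holds as a modest, inexpensive improvement, worth considering. As written, the rules can lose off-drug scores that the analysis by allocation would use, and LOCF would then fill them. If completeness is counted over all 120, the same losses draw on the allowance of 24.

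The size is unknown and probably small. Every loss rate and score difference used here is an assumption. Under them, the 80% verdict changes noticeably only when other loss is near 15%, and an arm mean moves by 0.01 to 0.05 SD. The comparison also takes everyone who stops the drug as willing to supply a week-7 score, which is optimistic for people who refuse it. The planned comparison of dropout rates and reasons by arm would make the loss visible but would not recover the scores.

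**What to change.** - **Safety and adverse events:** replace withdrawal from the trial with discontinuation of study drug. Define suspension of a participant as interruption of the drug with visits continuing. When to stop the drug remains the investigator's decision.
- **Rejection criteria:** remove unwillingness to take the drug as a ground.
- **Follow-up:** after drug stop, keep the three scales at the remaining scheduled visits up to week 7, unless the participant withdraws consent, dies or is medically unable.
- **CRF:** record the date and reason for drug stop separately from the date and reason for the end of assessment.

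The cost is wording in two sections, fields for two dates and two reasons, and a few off-drug visits that are already on the schedule. According to Trial status, recruitment began on 6 May 2017 and completion is due by December 2018. The benefit is therefore limited to participants still in follow-up and to the definitive trial that this pilot is meant to inform.

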### Data management and statistical analysis

The clinical data management system (http://www.tcmcec.net/) will be used to collect and manage the data. All data from the completed CRFs will be imported into the system twice by two independent data entry clerks to ensure the accuracy. The database will be locked when the principal investigators and statisticians check the data. The original medical records will be archived and saved in the unit responsible for 5 years after the completion of the trial.

All statistical analyses will be performed by an independent statistician blinded to the allocation, using the Statistical Analysis System (SAS, Version 9.2, Institute Inc., Cary, NC, USA) and assuming a two-sided test and a 0.05 level of significance. Based on the strict principle of intention-to-treat (ITT), the outcome measurements will be analysed using a full analysis set (FAS), which means the data of the participants will be analysed according to their original allocation, regardless of the treatment they actually received, withdrawals, losses to follow up, or crossovers. The last-observation-carried-forward (LOCF) method will be used for missing data, and safety outcomes will be analysed using safety sets (SS). Quantitative data will be analysed using the *t* test and analysis of variance (ANOVA). Enumeration data will be analysed using the chi-square test or non-parametric tests. We will use the paired *t* test to analyse significant differences between pre and post treatment. The total dropout rate in each group will be analysed using the chi-square test or Fisher’s exact test. Moreover, the reasons for dropouts will also be descriptively analysed and compared between the two groups. For the safety analysis, the incidence rate of adverse events will be evaluated using the chi-square test and described in a list.

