### Quality control

Quality control will be performed as followsRequest for the investigators:

The investigators must possess the qualifications and abilities needed to conduct the trial and will not be continually changed. The principal investigators will ensure the trial is conducted according to the standard operating procedure. A project manager at each site will be responsible for the quality of the research.2.Quality control throughout the entire process of the trial:

Before the trial, investigators will receive pre-trial training on patient screening, data filling, drug use, adverse event (AE) reporting and other matters. During the trial, the investigators will confirm that the participants have received the drugs on time and record the receipt on the medication record form. Those patients who do not take the drugs at the appropriate time will be encouraged to do so, and their reasons will be recorded in detail. Trial supervisors will visit each site regularly to check the case report forms and informed consent to ensure that the trial is strictly following the protocol. The investigators will take measures (to schedule further visits and follow-ups) to keep the incidence rate of dropout within 20%. The number of withdrawals, dropouts, and cases of compliance will be recorded in detail. The trial data will be entered into the database within 2 weeks of being collected. After the trial, all the data will be checked by the quality controller, principal investigator, and statisticians [2].

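### LOCF is fixed as the missing-data method for scales measured at five time points, and can bias the week-7 arm difference that is meant to inform future trials

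*Protocol article*

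**What the plan says.** Under Data management and statistical analysis, the protocol article says that "The last-observation-carried-forward (LOCF) method will be used for missing data". The sentence is not limited to a scale, visit or analysis, and no alternative or sensitivity analysis is named. The same section analyses the full analysis set by original allocation, keeping withdrawals and losses to follow-up, with t tests and ANOVA at a two-sided 0.05 level. Dropout rates and reasons are to be compared between arms.

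Outcome measures sets the schedule: "Each of the above scales will be completed on the day of enrolment and at the 2nd, 4th, 6th, and 7th weeks". It adds that "we will mainly focus on the data from the day of enrolment and the 7th week", and that the investigators will also look for an inflexion point, "which refers to the time point when the clinical symptoms of QS&BSS changes during the intervention", to choose the measurement time for a definitive trial. It sets the feasibility threshold: "Data completeness ≥ 80% is required for an outcome to be considered for definitive trials".

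Quality control describes measures "to keep the incidence rate of dropout within 20" per cent. Sample size says that 60 per group was not calculated and that the results will support the sample size of future trials.

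**The concern.** LOCF replaces each missing week-7 score with the last one recorded. That is harmless for the arm means only if nothing further would have happened to the people who left. The protocol expects movement: it measures four times after enrolment and looks for the point at which symptoms change. Someone who leaves after week 2 is held at a week-2 score and counted as a week-7 result.

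If dropout reaches the 20% that the protocol aims not to exceed, 12 of 60 participants per arm could carry such a value. The arm with more dropout, or with more improvement still to come, is held back more. The between-arm estimate can then move either way, and this estimate is one of the products that the pilot hands on for sample-size planning. The intermediate scores that a better analysis needs are already scheduled.

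**Working it through.** There is no figure in the protocol to reproduce: it states no effect size, SD, power or expected dropout by arm. The check therefore asks how far LOCF moves the week-7 difference under stated assumptions.

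**Inputs from the protocol article:** 60 per arm; scores at weeks 0, 2, 4, 6 and 7; week 7 as a main time point; LOCF; t test; two-sided 0.05.

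**Assumptions, not in the protocol:** improvement is linear to week 7; SD is 1 at each visit; correlation between visits is 0.6 (this affects error rates but not the means below); dropouts' last visits are split equally over weeks 0, 2, 4 and 6; dropout is unrelated to outcome unless stated.

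**Formula.** Let m be an arm's true improvement at week 7 (in SD), d its dropout proportion, and g the average share of improvement still to come at the last visit. Then:

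LOCF mean improvement = m × (1 − d × g)

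For a linear course, g = (7/7 + 5/7 + 3/7 + 1/7) / 4 = 16/28 = 0.571.

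**True difference 0.50 SD (improvement 1.0 against 0.5):**
- 20% dropout in both arms: 0.50 × (1 − 0.20 × 0.571) = 0.443. Power at 60 per arm falls from 0.78 to 0.68.
- 10% on XFZYC, 30% on placebo: 1.0 × 0.943 − 0.5 × 0.829 = 0.529, an overstatement.
- 30% on XFZYC, 10% on placebo: 1.0 × 0.829 − 0.5 × 0.943 = 0.357, an understatement.

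**No true difference (same improvement m in both arms).** The spurious difference is m × g × (difference in dropout):
- 5% against 20%, m = 0.8: 0.8 × 0.571 × 0.15 = 0.069 SD. Simulated type I error was 6.9%.
- 10% against 30%, m = 1.2: 1.2 × 0.571 × 0.20 = 0.137 SD (0.13 to 0.14 in simulation). Simulated type I error was 10.5%.
- 10% against 15%, m = 0.8: 0.8 × 0.571 × 0.05 = 0.023 SD. Simulated type I error was 4.6%, so no inflation was seen.
- 20% in both arms: 0. Simulated type I error was 4.6%.

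**Shape of the course.** If improvement is complete by week 4, g = (1 + 0.5 + 0 + 0)/4 = 0.375, and 20%/20% dropout reads 0.50 as 0.50 × 0.925 = 0.462. If improvement starts only after week 4, g = (1 + 1 + 1 + 1/3)/4 = 0.833, and it is read as 0.417. If scores do not change and dropout is unrelated to outcome, there is no bias.

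**Dropout more likely with worse observed scores** (simulation, linear course, true 0.50 SD): LOCF gives 0.43 at 20%/20%, 0.59 at 10%/30% and 0.26 at 30%/10%. In a separate simulation of this kind at nominal 10%/30%, LOCF gave 0.61 while a likelihood estimate using all observed visits gave 0.50.

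**Consequence for planning.** Required sample size varies with 1/(difference)². Reading 0.50 as 0.443 multiplies it by (0.50/0.443)² = 1.27; reading it as 0.357 multiplies it by 1.96; reading it as 0.529 multiplies it by 0.89.

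**Trajectory.** In the XFZYC arm with a linear course and 20% dropout, true improvement of 0, 0.286, 0.571, 0.857 and 1.000 becomes 0, 0.271, 0.529, 0.771 and 0.886. Later slopes flatten.

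**The case against.** The strongest defence is that the trial's primary aim is untouched. Outcome measures counts only reported and recorded values as complete, so carried-forward values cannot help a scale to pass the 80% threshold. That stands, and it limits the severity.

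It is also fair that the bias is conditional. The larger spurious effects need a threefold or fourfold imbalance in dropout, which nothing in the protocol predicts. The planned comparison of dropout by arm could reveal such an imbalance, although it would not correct the estimate. An analysis plan that is not shown could add sensitivity analyses, but the main method stated here would still be LOCF.

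A reader might infer more than the documents support:
- That LOCF favours XFZYC. The direction depends on which arm loses more, and with equal dropout a true effect is understated.
- That response-related dropout is built in, because participants are "encouraged to contact the investigators if they have any uncomfortable feeling or if they think the drugs are not helpful". This applies to both arms of a trial described as double-blind and says nothing about withdrawal. It makes such dropout plausible, no more.
- That the inflexion point moves. The protocol does not say that carried-forward scores enter that assessment; it only fails to exclude them. In the equal-dropout calculations slopes flattened but the bend stayed where it was.
- That the SD for future planning is badly distorted. Simulated SDs were 1.01 to 1.07 against a true 1.00.
- That the intermediate visits serve only to supply carried-forward values. They also serve the inflexion-point aim, and ANOVA is named without being restricted to week 7.

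**Conclusion.** The point holds in conditional form. LOCF is a poor main method here because the protocol expects scores to change over the visits and already collects the data that a better method needs. If scores keep changing after dropout, the week-7 difference can be biased. Under the assumed linear course, 0.50 SD becomes about 0.44 SD at 20% dropout in both arms. No effect becomes about 0.07 SD (5%/20%) to 0.13–0.14 SD (10%/30%, type I error about 10%). The bias is close to zero when there is no true effect and dropout is equal and unrelated to outcome. All these sizes rest on assumed improvement, dropout and trajectory, since the protocol gives none.

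This should be fixed, because the estimates are to feed the sample size of later trials. It does not undermine the completeness objective, so it is not critical for a feasibility pilot.

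**What to change.** Replace the LOCF sentence with wording such as: each scale will be analysed with a likelihood-based repeated-measures model on observed scores at weeks 2, 4, 6 and 7, adjusted for the enrolment score, with the week-7 difference between arms as the main contrast. Multiple imputation is an acceptable alternative. Keep LOCF at most as a sensitivity analysis. State that the trajectory used for the inflexion point is described from observed data or model visit means, not from carried-forward scores. The covariance structure, further covariates and other sensitivity analyses can be left to the analysis plan.

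The cost is a change of wording and slightly more analysis work, with no new data or participants. The replacement relies on data being missing at random given the observed scores, which cannot be verified from the data and should be stated.

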### Randomisation

A total of 120 eligible participants will be allocated to either the XFZYC group or placebo group in a 1:1 ratio using a block randomisation method. The central randomisation system will be used and performed by the Clinical Evaluation Centre of China Academy of Chinese Medical Sciences, which will also maintain the randomisation lists.

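### The between-arm comparison of the scales is not adjusted for the enrolment score, although every scale has one, so precision is given up for nothing

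*Protocol article*

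**What the plan says.** In the protocol article, Data management and statistical analysis, the rule for continuous outcomes is "Quantitative data will be analysed using the *t* test and analysis of variance (ANOVA", with testing "assuming a two-sided test and a 0.05 level of significance". The same paragraph adds "We will use the paired *t* test to analyse significant differences between pre and post treatment". That is the only named analysis that expressly uses the enrolment score, and it compares time points rather than arms. No covariate, ANCOVA or mixed model is named anywhere in the article.

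Under Outcome measures, "Each of the above scales will be completed on the day of enrolment and at the 2nd, 4th, 6th, and 7th weeks", and of these visits "we will mainly focus on the data from the day of enrolment and the 7th week".

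Under Sample size, the number was not derived: "we adopted this pilot study with an appropriate sample size of 60 participants per group". The section then gives the pilot a planning role: "The outcomes of this trial will provide data support for the calculation of the appropriate sample size for future clinical trials".

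**The concern.** The plan collects an enrolment value of each scale and treats it as one of its two key measurements, then names between-arm methods that do not adjust for it. It also leaves open whether the t test is applied to the week-7 score or to the change from enrolment. Under either reading, if enrolment and week-7 scores are positively correlated, the estimate of the difference between XFZYC and placebo has a wider confidence interval than the same data could give.

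What is at stake is efficiency, not validity. The primary objective is the feasibility and acceptability of the outcome measures, judged by data completeness of at least 80%, and this point does not touch that. It does touch the between-arm estimates the plan commits to testing, and the variance information that a definitive trial would take from this pilot.

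**Working it through.** **The plan's own figure.** 60 per arm cannot be reproduced, because the article gives no target difference, SD or power and says that the size could not be calculated. There is nothing to check it against, so the comparison below is between methods of analysis.

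**Inputs.** From the document: 60 per arm, 1:1 allocation, two-sided 0.05, every scale measured at enrolment and week 7. Assumed: the correlation r between the enrolment and week-7 score of a scale (0.3, 0.5, 0.7), and equal SDs at the two time points, set to 1.

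**Formulas.** The variance of the between-arm difference is proportional to the squared SD of the quantity analysed:
- week-7 score: SD² = 1
- change from enrolment: SD² = 2(1 − r)
- ANCOVA residual: SD² = 1 − r²

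So ANCOVA relative to the week-7 score is 1 − r². Relative to change it is (1 − r²) / [2(1 − r)] = (1 + r)/2. Both are below 1 for any r strictly between 0 and 1.

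| r (assumed) | ANCOVA / week-7 score | ANCOVA / change score |
|---|---|---|
| 0.3 | 1 − 0.09 = 0.91 | 1.3/2 = 0.65 |
| 0.5 | 1 − 0.25 = 0.75 | 1.5/2 = 0.75 |
| 0.7 | 1 − 0.49 = 0.51 | 1.7/2 = 0.85 |

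At r = 0.5, an unadjusted analysis would need 120/0.75 = 160 patients to match ANCOVA on 120.

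These are large-sample ratios. Estimating the slope on the enrolment score multiplies the ANCOVA variance by about 1 + 1/(120 − 4) = 1.009, which is negligible here.

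**As interval width.** With 60 per arm, the 95% half-width for the raw week-7 difference is 1.96 × √(2/60) = 0.36 SD. Multiplying by the ANCOVA residual SD (0.954, 0.866, 0.714) gives 0.34, 0.31 and 0.26 SD.

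**As power.** For an assumed difference of 0.5 SD with 60 per arm:

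| r (assumed) | t test, week-7 score | t test, change | ANCOVA |
|---|---|---|---|
| 0.3 | 78.2% | 63.9% | 81.9% |
| 0.5 | 78.2% | 78.2% | 88.5% |
| 0.7 | 78.2% | 94.2% | 97.0% |

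**For planning a later trial.** For the same assumed 0.5 SD at 80% power, and r = 0.3 / 0.5 / 0.7, n per arm is:
- week-7 t test: 63 / 63 / 63
- change-score t test: 88 / 63 / 38
- ANCOVA: 58 / 48 / 33

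Which row applies depends on how the definitive trial will be analysed, and the article does not say.

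**The case against.** **The trial is a feasibility pilot, and the test is valid.** Both are true. No efficacy hypothesis or power is claimed, and a t test in a randomised comparison is not biased by the lack of adjustment. This limits the weight of the point but does not remove it, because the plan still commits to between-arm tests and the improvement needs no new data.

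**ANOVA may contain more than treatment.** The article does not list its factors. With two arms, a one-way ANOVA only repeats the t test, so disease, site or time may be intended. That is possible, but none of these is an adjustment for the enrolment score. The detail might sit in an analysis plan that is not shown, but the article does name its methods, and a baseline-adjusted one is not among them.

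**The correlation is unknown.** This stands. At r = 0.3 the gain over raw week-7 scores is small (0.91). Entry requires a diagnostic-scale score of at least 20; if that score tracks the outcome scales, the enrolment range is restricted and r may be low. The figure of 160 is one point in a wide range. A low r weakens the case against a week-7 t test but strengthens it against a change-score t test.

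**Stronger readings that a reader might infer.**
- *The definitive trial will be sized on too large an SD.* The Sample size section does not say which SD will be carried forward. An unadjusted SD is the right one for an unadjusted trial. Both scores are collected, so r and the residual SD can be computed whatever test is named.
- *Chance baseline imbalance adds a further error.* With 60 per arm, 95% of chance differences in the enrolment means lie within 1.96 × √(2/60) = 0.36 SD, which at r = 0.5 shifts the raw week-7 difference by 0.18 SD. That variation is already inside the unadjusted standard error, so it is not an additional bias.
- *Disease and hospital are wrongly ignored or left unstratified.* The article gives no figure for how strongly either predicts the scores. Its silence on strata is what a condensed article commonly leaves to the full protocol. Its Discussion also plans subgroup comparisons by disease.

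**Conclusion.** The point holds as a matter of efficiency. The plan names only unadjusted between-arm methods for scales whose enrolment values it collects and treats as central. For correlations of 0.3 to 0.7 with equal SDs (both assumptions), ANCOVA would reduce the variance to 0.91 to 0.51 of that from week-7 scores, or 0.65 to 0.85 of that from change scores. The direction holds for any correlation strictly between 0 and 1; the size depends on a value the document does not give.

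The documents do not support saying that the analysis is invalid, that the primary feasibility conclusion would change, or that the later trial's sample size is already compromised. The change is worth making because it costs almost nothing.

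**What to change.** In Data management and statistical analysis, state that the week-7 difference between arms on each scale will be estimated by ANCOVA, or by the week-7 contrast of a mixed model, adjusting for that scale's enrolment score, and reported with a 95% CI. Qualifying disease and hospital may be added as covariates; this is optional.

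Because the pilot is to support a later sample-size calculation, add that the raw SD, the residual SD and the enrolment to week-7 correlation will be reported for each scale. The planners of the definitive trial can then take the SD that matches the analysis they choose.

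Cost: one or two sentences in the plan, settled before unblinding. No additional data, visits or patients are needed.
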